## Abstract

**Background:**

Cancer screening nonadherence persists among adults who are deaf, deafblind, and hard of hearing (DDBHH). These barriers span individual, clinician, and health care system levels, contributing to difficulties understanding cancer information, accessing screening services, and following treatment directives. Critical communication barriers include ineffective patient-physician communication, limited access to American Sign Language (ASL) cancer information, misconceptions about medical procedures, insurance navigation difficulties, and intersectional barriers for multiply marginalized individuals.

**Objective:**

This randomized controlled trial addresses these barriers by implementing the first videoconference-based study of ASL-fluent community health navigators (ASL-CHNs) to improve cancer screening adherence among adults who are DDBHH. The study tests whether ASL-CHN intervention results in greater adherence to cancer screening guidelines, improved patient-physician communication ratings, and increased cancer knowledge compared to standard care.

**Methods:**

The study uses a videoconference-delivered, block-randomized design stratifying 200 participants who are DDBHH by age and sex, with 100 participants assigned to the ASL-CHN intervention and 100 to standard care. All participants are confirmed as nonadherent to at least 1 of 5 age-appropriate cancer screening guidelines recommended by the United States Preventive Services Task Force for breast, cervical, colorectal, lung, and prostate cancers. Recruitment occurred nationwide through multiple strategies including prior study participants, community partners, and major community events. The intervention arm receives support from specially trained ASL-CHNs over several months, accommodating lengthy scheduling processes for cancer screenings. Primary outcomes measure completion of age- and risk-appropriate cancer screening, with prostate cancer focusing on shared decision-making participation. Secondary outcomes assess patient-physician communication using the validated National Cancer Institute’s Health Information National Trends Survey (NCI-HINTS) Patient Centered Communication questionnaire in ASL. Tertiary outcomes examine cancer knowledge through validated measures. The analysis uses intent-to-treat methodology using multivariable logistic regression, accounting for potential clustering effects and anticipated 25% attrition.

**Results:**

As of August 2025, more than 75% of the target enrollment has been achieved. Preliminary data indicate that the intervention group is consistently outperforming the standard care group in cancer screening adherence, supporting the study hypothesis that ASL-CHNs are effective in promoting cancer screening adherence among previously nonadherent participants who are DDBHH.

**Conclusions:**

The ASL-CHN intervention represents an accessible, scalable solution for reducing cancer screening disparities. By combining personalized navigation with ASL-fluent community health support through videoconferencing, this intervention addresses limitations of previous screening programs that lacked accessible support. If successful, the ASL-CHN model could provide health care providers with a practical, recommendable option for patients who are DDBHH requiring navigator support that can be done remotely through videoconferencing, potentially improving early detection rates and reducing cancer mortality in this underserved population while advancing accessible care delivery.

**Trial Registration:**

ClinicalTrials.gov NCT06492993; https://clinicaltrials.gov/study/NCT06492993

**International Registered Report Identifier (IRRID):**

DERR1-10.2196/65078

## Introduction

### Background

Cancer health disparities are common issues across underserved populations that are driven by social determinants of health. As detailed in *Community Health Navigators for Cancer Screening among Deaf, Deafblind, and Hard of Hearing (DDBHH) Adults Who Use American Sign Language* [1], the barriers to health screening and treatment are multilevel, persisting at the individual, clinician, and health care system levels, and can affect patients who are deaf, deafblind, and hard of hearing (DDBHH) across their lifespan. There are documented reports of difficulties in understanding cancer health information in print [1-3], accessing clinical services for screenings [1,4-7], and understanding and following treatment-related directives if the screening results in a cancer diagnosis [8]. Communication difficulties contribute to delayed diagnoses, exclusion from clinical trials, and differential treatment that result in poorer cancer outcomes for deaf and hard of hearing patients.[9]. The complexity of the field of oncology and rapidly expanding associated vocabulary further exacerbates these health inequities. Despite the availability of basic cancer information in American Sign Language (ASL) that helps improve cancer literacy for people who use ASL, the complex nature of cancer prevention, detection, and treatment creates barriers to care for individuals who are DDBHH that even exceed the challenges of hearing non-English speaking populations. The current standard of care for individuals who are DDBHH may include visiting doctors alone, with a sign language interpreter who may or may not be capable of interpreting at the level needed in the complex oncology environment, or with a family member.

Community health workers (CHW) and navigators (CHN) are becoming more common in health care systems, based on research that confirms their ability to help patients more successfully navigate through their health care system [10]. For example, the Baltimore HEARS project demonstrated the success of a CHW-delivered intervention program for older adults who already had considerable spoken and written language proficiency because their hearing loss occurred later in life [10]. The CHW hearing loss program relied upon materials that are not easily accessible to people who rely upon ASL as their preferred form of communication. Thus, the focus of this research project was to create and evaluate a training program to prepare CHNs to work with individuals who are DDBHH, the majority of whom use ASL as their primary means of communication and have limited English language skills.

For the vulnerable group of people who are DDBHH in need of cancer screening and preventive care, an intervention delivered by CHNs who use ASL and ASL-based teaching materials offers an excellent source of relief and support in the face of barriers to health care. This paper describes the development and evaluation of a CHN intervention that is accessible in ASL as a logical strategy for reducing barriers to improved health care access for people who are DDBHH.

### Trial Aim

The aim of this trial is to implement the first randomized controlled trial of a DDBHH CHN intervention that is (1) accessible in ASL and English, (2) easy to understand, (3) relevant to the experiences of people who are DDBHH, (4) inclusive of videoconferencing for face-to-face ASL communication, and (5) easy to use. The intervention will be evaluated using multiple criteria to assess the effectiveness of the navigator in guiding patients who are DDBHH through the cancer screening process.

### Hypothesis

This study tested the hypothesis that the use of ASL-fluent CHNs (ASL-CHNs) will result in:

Patients who are DDBHH demonstrating greater adherence to cancer screening guidelines compared to those assigned to the standard of care group (without access to this program’s trained CHNs).Higher patient-physician communication ratings by patients who are DDBHH compared to those assigned to the standard of care group.A direct relationship between increased cancer knowledge and cancer screening adherence compared to the standard of care group.

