### Outcome Measures

Bilingual ASL-English measures (eg, sociodemographics, cancer screening knowledge, and patient-physician communication) will be administered at screening and again after the fourth month or by 11 months for comparison.

The primary outcome is completion of age- and risk-appropriate recommended cancer screening, which is a binary variable measured at the closeout follow-up for breast, cervical, colon, and lung cancer. For prostate cancer screening, the primary endpoint is participation in shared decision-making with the clinician.

The secondary outcome is patient-physician communication measured by the National Cancer Institute’s Health Information National Trends Survey (NCI-HINTS) Patient Centered Communication questionnaire that was validated in ASL [12]. The set of items for the Patient Centered Communication score are outlined in Textbox 1.

Items for the Patient Centered Communication score.How often did the doctors, nurses, or other health care professionals you saw during the past 12 months do each of the following:a) Give you the chance to ask all the health-related questions you had?b) Give the attention you needed to your feelings and emotions?c) Explain things in a way you could understand?d) Spend enough time with you?c) Involve you in decisions about your health care as much as you wanted?d) Make sure you understood the things you needed to do to take care of your health?e) Help you deal with feelings of uncertainty about your health or health care?

The tertiary exploratory outcome is cancer knowledge and includes two questions:

It seems like everything causes cancer.How much do you think that gaining weight in adult life can influence whether or not a person will develop cancer?

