### Analysis Plan

All analyses will be conducted using SAS 9.4, with a 2-sided *P* value <.05 considered statistically significant. The DDBHH sample size sufficiently powers the detection of differences in the primary study outcomes. Based on a 2-sided Z-test with unpooled variance and a significance level (α) of .05, our study sample of 200 participants with 100 in each group will achieve at least 80% power to detect a difference in proportions of 14%-17% in the group proportions of adherence (ie, almost 82%-92% adherence in the intervention group, assuming 65%-78% of the eligible participants in the standard of care group have obtained age- and risk-appropriate cancer screening at follow-up) based on previous studies. Univariate statistics for baseline characteristics will be computed with stratification by group, as will patient-physician communication and cancer knowledge at baseline and follow-up. Bivariate analyses will examine group differences in patient characteristics. We will primarily use an “intent-to-treat” approach, using multivariable logistic regression to evaluate whether the recommended cancer screening rates are higher in the intervention group than in the standard of care group. Though we do not expect strong clustering effects with CHNs, we will account for potential clustering using generalized estimating equations, with regression models including group assignment and adjusting for relevant covariates.

If a sufficient number of participants cross over from the standard of care arm to the intervention group, we will conduct sensitivity analyses to assess whether they performed better than the standard of care group. Despite efforts to maximize retention, we anticipate approximately 25% attrition, which may introduce bias. To address this, we will determine if dropouts differ between randomized groups, adjust for any resulting imbalances in baseline covariate distributions, and perform sensitivity analyses under different assumptions (missing completely at random, participants who dropped out would have been responders, or participants who dropped out would have been nonresponders).

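### The third hypothesis is stated as two different questions, and the version in the Hypothesis section is an association that randomisation does not protect

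*Protocol article*

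**What the plan says.** The Objective in the protocol article's abstract lists what the trial tests. After adherence come "improved patient-physician communication ratings, and increased cancer knowledge compared to standard care". Knowledge is the outcome and arm is the exposure.

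The Hypothesis section gives the third expected result of using the navigators as "A direct relationship between increased cancer knowledge and cancer screening adherence compared to the standard of care group". Here knowledge is the explanatory variable, adherence is the outcome, and the role of the comparison with standard care is unclear.

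Other sections bear on which is meant:

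- Outcome Measures: "The tertiary exploratory outcome is cancer knowledge and includes two questions". The bilingual measures, knowledge among them, "will be administered at screening and again after the fourth month or by 11 months for comparison".
- Analysis Plan: univariate statistics are planned by group, "as will patient-physician communication and cancer knowledge at baseline and follow-up". The screening outcome is analysed by logistic regression and generalised estimating equations, "with regression models including group assignment and adjusting for relevant covariates".
- Analysis Plan: the power statement covers adherence only.

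**The concern.** The two statements can be true or false independently. If better-informed people are screened more often in both arms and the navigator leaves knowledge unchanged, the Objective's claim is false although a direct relationship is found. If the navigator raises knowledge but knowledge has no bearing on screening, the reverse holds. What the trial concludes about knowledge therefore depends on which section the analyst follows.

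The versions also differ in evidential standing. The Objective's version compares randomised groups. The Hypothesis version relates a change in knowledge, measured after randomisation, to screening, which also happens after randomisation. The closing knowledge measure falls after month 4 or by month 11, often after screening has happened, so being screened may itself have raised knowledge. Exposure adds to this. Under Study Arms, intervention participants who are unscreened at 4 months get up to 7 more months of navigator contact, while standard-care participants who have not scheduled by then are recorded as failures. Navigator contact thus depends on screening status in one arm only, which could by itself make the association differ between arms.

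**Working it through.** **1. The plan's own figure.** From the Analysis Plan: 100 per arm, two-sided α = 0.05, unpooled Z-test, adherence 65% vs 82% or 78% vs 92%. Power = Φ(d / √[(p₁(1−p₁) + p₂(1−p₂))/n] − 1.96).

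- 65% vs 82%: 79.3%
- 78% vs 92%: 80.7%

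The stated 80% is reproduced to within rounding of the inputs. It concerns adherence only, so no stated power is contradicted by what follows.

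**2. The candidate questions.**

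| Reading | Source | Quantity | Randomised comparison? |
|---|---|---|---|
| A | Objective | Difference between arms in follow-up knowledge | Yes |
| B | Hypothesis, as a simple association | Common slope of adherence on knowledge | No |
| C | Hypothesis, taking the comparison with standard care literally | Difference between arms in that slope (arm-by-knowledge interaction) | No: the slopes compared are themselves associations |

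Listing knowledge itself as an outcome, and summarising it by group, fits A only.

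**3. What each reading could detect.** Inputs from the plan: the adherence rates above, and n = 100 per arm, or 75 after the anticipated 25% attrition. *Assumed, not in the article:* knowledge change is a continuous standardised score with the same SD in both arms. The multiplier for 80% power is 1.96 + 0.84 = 2.80.

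- A: d = 2.80 × √(2/n)
- B: SE of the log odds ratio per SD = 1/√[n·p_c(1−p_c) + n·p_i(1−p_i)]
- C: SE of the log ratio of odds ratios per SD = √[1/(n·p_c(1−p_c)) + 1/(n·p_i(1−p_i))]

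Worked case for C at n = 100, 65% vs 82%: √(1/22.75 + 1/14.76) = 0.334. The detectable ratio is exp(2.80 × 0.334) = 2.55. Power for a ratio of 2 is Φ(0.693/0.334 − 1.96) = 54.5%.

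| n per arm | Rates | A: SD | B: OR per SD | C: SE | C: ratio of ORs per SD | C: power at ratio 2 | C: power at ratio 3 |
|---|---|---|---|---|---|---|---|
| 100 | 65/82 | 0.40 | 1.58 | 0.334 | 2.55 | 54.5% | 90.8% |
| 100 | 78/92 | 0.40 | 1.76 | 0.441 | 3.44 | 34.9% | 70.3% |
| 75 | 65/82 | 0.46 | 1.70 | 0.386 | 2.95 | 43.5% | 81.2% |
| 75 | 78/92 | 0.46 | 1.92 | 0.509 | 4.16 | 27.5% | 57.9% |

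Columns A, B and C (ratio) give the effect detectable with 80% power. With baseline adjustment and an assumed baseline-to-follow-up correlation of 0.5, A improves by √(1 − 0.25) to 0.34 SD (100 per arm) or 0.40 SD (75 per arm).

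**4. Sensitivity to scoring.** Suppose instead that knowledge improvement is binary, present in 30% or 50% of each arm, with a control-arm odds ratio of 1. Wald power for C is then 10–17% at a ratio of 2 and 15–34% at a ratio of 3 with 100 per arm, and 9–14% and 13–27% with 75 per arm. Likelihood-ratio simulation at 50% prevalence, over both sample sizes, gives 13–19% at a ratio of 2 and 22–35% at a ratio of 3.

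**5. How far the readings can part.** Illustration with assumed effects at 75 per arm:

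- *No navigator effect on knowledge, OR 2 per SD in both arms.* B is significant with probability Φ(0.693/0.189 − 1.96) ≈ 96% (65/82) or Φ(0.693/0.233 − 1.96) ≈ 84% (78/92). A is significant in 5% of trials, by construction.
- *Navigator adds 0.5 SD, knowledge unrelated to screening.* A is significant with probability Φ(0.5/0.163 − 1.96) ≈ 86%, and B at the 5% error rate.

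**The case against.** Outcome Measures already labels knowledge tertiary and exploratory, and the article's stated conclusions concern adherence, not knowledge. Little is said to rest on this outcome. That stands and limits the weight of the point. It does not remove it: the Hypothesis section lists the relationship beside the other two hypotheses without that label.

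A reader might infer that the third hypothesis is practically untestable at this size. The article does not support that. It names no interaction, and association or mediation are equally possible readings. A common slope is detectable at an odds ratio of about 1.6 to 1.9 per SD, and even the interaction has 58% to 91% power at a ratio of 3 per SD. Scoring, spread and effect sizes are not given, and step 4 shows how much the answer moves with scoring. Low power for an exploratory interaction is also not an error in itself.

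A reader might also infer that the plan has no analysis for knowledge. The by-group summaries are a descriptive analysis that fits the Objective, and a model for a tertiary outcome may sit in a full protocol or analysis plan not shown. Its absence from the article is not part of this point.

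The illustration in step 5 shows only that two different questions can have different answers. It predicts nothing about this trial.

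Study Integrity also mentions knowledge measures at 2 weeks, 2 months and 4 months. Using those taken before screening would reduce reverse causation, but not confounding.

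Finally, the Discussion stresses mechanisms of action, so a knowledge-adherence question may be intended. It can be kept, provided it is labelled for what it is.

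**Conclusion.** The contradiction is in the printed text and needs no assumption: the Objective and the Hypothesis section state different questions, and the outcome list and by-group summaries match only the Objective. It follows equally directly that the Hypothesis version relates two post-randomisation variables and is open to confounding and reverse causation. It could therefore be supported with no navigator effect on knowledge.

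The power statement is conditional. Under the interaction reading, with an assumed continuous score, power is about 27% to 55% for a ratio of odds ratios of 2 per SD at 75 to 100 per arm. It is lower if knowledge is scored as a binary improvement. The point is worth correcting, but it is confined to what the trial can say about knowledge.

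**What to change.** Restate the third hypothesis to match the Objective: cancer knowledge at follow-up is higher with the navigator than with standard of care. Estimate it as the between-arm difference adjusted for the baseline knowledge already collected, and keep it exploratory as in Outcome Measures.

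If the link between knowledge and adherence remains of interest, specify it separately as an association or a mediation analysis. Describe it as non-randomised and exploratory, report it with a confidence interval, and attach no confirmatory claim.

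Record the date of and reason for the change. The Results section says preliminary adherence by arm has already been seen, so this is a late change and should be disclosed as such. Making it before the final analysis still prevents the reading from being chosen on the results.

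The cost is one reworded hypothesis and one regression on existing data. The sponsor gives up a hypothesis-level claim that knowledge explains adherence.

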## Methods

### Ethical Considerations

The protocol (IRB-FY21-120) was reviewed and approved by Gallaudet University’s Institutional Review Board (IRB) prior to recruitment.

Eligible participants undergo a consenting process with an ASL-fluent clinical research coordinator who explains the study purpose and expectations in both English (fourth grade reading level) and ASL (using common sign vocabulary while minimizing fingerspelling). Participants understand they must share that the cancer screening appointment has been completed and its results with researchers for evaluation purposes, since the evaluation of the experimental arm’s intervention ended at the point of completed screening.

All participants receive tokens of appreciation. Two equal-sized financial gifts were originally approved by the IRB. However, as long-term retention in the study proved to be a concern, an alternate gifting strategy was requested and approved by the IRB: a smaller gift after baseline data collection ($25) and a larger one after completing the final assessment ($75) to recognize the greater value of their persistence in the study.

### Study Design

This study uses a parallel group, block-randomized design with 1:1 allocation stratifying 200 participants who are DDBHH by age and sex, with 100 participants assigned to the ASL-CHN intervention and 100 to standard of care.

All participants were confirmed as being nonadherent to at least 1 of 5 age-appropriate cancer screening guidelines recommended by the United States Preventive Services Task Force (USPSTF [11]). Nonadherence to the guidelines was confirmed during the recruitment process and again during the gathering of baseline data postrandomization. If a randomized participant either realized that they had indeed already been screened for all recommendations or were screened during the interval between recruitment and baseline data collection, they were removed from the study. In these instances of removal, those participants were moved to a separate database for future studies that they may be eligible for.

No significant protocol modifications have been implemented since trial commencement.

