### Sample Recruitment

Multiple recruitment strategies were used to attract a diverse sample of individuals who are DDBHH nationwide. One strategy was to contact individuals who are DDBHH who had participated in prior studies conducted by this paper’s senior Gallaudet University researcher. The prior study participants were reminded of their past study participation and asked if they would be willing to learn about a new research study that also had the potential to benefit the DDBHH community.

Another recruitment strategy was to work with community leaders across the nation to set up local recruitment events. A third was to attend major community events that attracted large groups from the community where study recruitment could be efficiently conducted. The recruitment and consenting process used for all of these strategies were comparable.

Those who indicated their interest in participating were asked a set of questions to determine their eligibility for the new study. Once their eligibility was confirmed, they were told a follow-up contact would be made to formally enroll them in the study. During the follow-up enrollment conversation, the participants’ eligibility was reconfirmed and then they were enrolled in the study and randomly assigned to a study arm based on their sex and age as previously decided by the randomization scheme.

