### Study Arms

#### Intervention Arm

In the intervention arm with videoconferencing, specially trained ASL-CHNs meet with participants over a period of up to 11 months. This extended timeframe is deliberately designed to accommodate the often-lengthy scheduling process for certain cancer screenings, which can take several months from initial referral to completion due to limited availability of specialists, preparation requirements, and health care system delays.

The intervention begins with an initial meeting to complete the consenting and randomization processes, gather baseline data, work with the participant to select the screening they would like to accomplish first, and provide directions on how to proceed with that screening. During the second meeting, about 2 weeks later, the ASL-CHN determines whether the screening has occurred or is scheduled and identifies any barriers encountered in making appointments or accomplishing the screening. If problems were encountered, the ASL-CHN engages in role-playing related to both the specific problem and commonly encountered problems during health care interactions.

All participants receive at least 4 months of intervention support. For those who have not completed screening by this 4-month assessment point, the study provides up to 7 additional months of support (for a total of up to 11 months). Throughout this period, the ASL-CHN continues to meet with participants to address emerging barriers, provide coaching through role-playing exercises, and offer support until screening is accomplished or until the maximum 11-month timeframe is reached.

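### Randomised participants are removed if a baseline check after randomisation finds them screened, which conflicts with the intent-to-treat analysis and can delete primary-outcome successes

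*Protocol article*

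**What the plan says.** All places are in the protocol article.

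- **Study Design** has nonadherence confirmed at recruitment and "again during the gathering of baseline data postrandomization".
- The same section gives two triggers for removal. The first is a discovery about the past: "If a randomized participant either realized that they had indeed already been screened for all recommendations". The second covers people who "were screened during the interval between recruitment and baseline data collection, they were removed from the study".
- On what follows removal, it says only that "those participants were moved to a separate database for future studies that they may be eligible for". No further follow-up or analysis of these people in this trial is described.
- **Sample Recruitment** describes an earlier check. In the follow-up enrolment conversation, the participants' "eligibility was reconfirmed and then they were enrolled in the study and randomly assigned to a study arm".
- **Intervention Arm** gives the timing for that arm: "The intervention begins with an initial meeting to complete the consenting and randomization processes, gather baseline data". **Standard of Care Arm** does not say when baseline is taken.
- The **abstract (Methods)** states: "The analysis uses intent-to-treat methodology using multivariable logistic regression". The **Analysis Plan** repeats the intent-to-treat approach. It plans sensitivity analyses for crossovers and dropouts and considers multiple imputation for missing data, but does not mention these removals.
- **Outcome Measures** defines the endpoint: "The primary outcome is completion of age- and risk-appropriate recommended cancer screening, which is a binary variable measured at the closeout follow-up". For prostate cancer the endpoint is shared decision-making.

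**The concern.** An intent-to-treat analysis keeps every randomised person in the assigned arm. A rule that takes people out on information gathered after assignment departs from this, whatever the analysis is called.

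Three features make it more than an ordinary late eligibility exclusion.

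- **The trigger resembles the outcome.** Both are a completed screening. The second trigger runs up to baseline, which the document places after randomisation. Someone screened between the two has met the primary endpoint, yet disappears from numerator and denominator.
- **The evidence standards differ.** Under Study Integrity, success must be documented. The removal rule states no evidence requirement, no test of the screening date against the randomisation date, and no judgement blind to arm.
- **The second trigger is loosely worded.** The first is limited to people up to date on all recommendations. The second does not repeat that limit. It could be read to remove someone who completed one screening and still qualifies through another.

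At stake is whether the set analysed in the primary comparison is the set randomised.

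**Working it through.** **1. The passages side by side**

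| Event | Treatment under Study Design | Treatment under intent-to-treat |
|---|---|---|
| All screening completed before randomisation, found out later | Removed | Exclusion defensible if it rests only on pre-randomisation facts and is judged alike in both arms |
| Screened between recruitment and randomisation | Removed | Same, provided the screening made the person ineligible |
| Screened between randomisation and baseline | Removed | Kept, and counted as a success |

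The third row is the clear error. The first two need a date and an arm-blind rule, and neither is stated.

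**2. The plan's own power figure**

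Inputs from the Analysis Plan: 100 per arm, two-sided alpha .05, unpooled Z-test, control 65% to 78%, intervention 82% to 92%, power at least 80%.

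Power = Φ(|p1 − p2| / √(p1q1/n + p2q2/n) − 1.96)

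- 65% v 82%: 0.17 / √(0.002275 + 0.001476) = 0.17 / 0.0612 = 2.776, so power is Φ(0.816) = 79.3%.
- 78% v 92%: 0.14 / √(0.001716 + 0.000736) = 0.14 / 0.0495 = 2.827, so power is Φ(0.867) = 80.7%.

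The stated power is reproduced to within a point and is not in dispute.

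**3. Illustration with no true effect**

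The text gives no removal counts, so the removed share r is an assumption. Suppose both arms have true rate p, a share r is removed from controls only, and every removed person would have been a success. The control rate becomes (p − r)/(1 − r), so:

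spurious difference = p − (p − r)/(1 − r) = r(1 − p)/(1 − r)

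| p | r = 5% | r = 10% |
|---|---|---|
| 65% | 0.05 × 0.35 / 0.95 = 1.8 points | 0.10 × 0.35 / 0.90 = 3.9 points |
| 78% | 0.05 × 0.22 / 0.95 = 1.2 points | 0.10 × 0.22 / 0.90 = 2.4 points |

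Starting from 100 per arm, let d be the spurious difference divided by its unpooled standard error. The two-sided rejection rate is Φ(d − 1.96) + Φ(−d − 1.96):

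- 5 controls removed: 5.8% (p = 65%) or 5.4% (p = 78%).
- 10 controls removed: 8.6% or 6.8%.
- 5 removed from each arm: difference 0, rejection rate 5.0%.

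**4. Illustration with the planned effect**

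Removing k would-be successes from an arm of 100 changes its rate from p to (100p − k)/(100 − k).

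| Removed | 65% v 82% (17.0 points) | 78% v 92% (14.0 points) |
|---|---|---|
| 5 controls only | 18.8 | 15.2 |
| 10 controls only | 20.9 | 16.4 |
| 5 intervention only | 16.1 | 13.6 |
| 10 intervention only | 15.0 | 13.1 |
| 5 from each arm | 17.9 | 14.7 |

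The sign depends on which arm loses more people. Equal removal is harmless under the null but still shifts a real effect.

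**The case against.** The strongest reply is that the damage may be very small.

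- **Much of the removal window precedes randomisation.** It opens at recruitment, which is an earlier contact than enrolment, and the first trigger concerns a fact already in existence. Such people were never eligible, and excluding them on pre-randomisation facts is accepted practice. This stands for those removals. It does not cover screening done after assignment, which the rule also captures.
- **The window after randomisation may be close to zero.** The Intervention Arm section puts consent, randomisation and baseline in one meeting. If controls have the same meeting, few outcome events can be lost. This too stands as a possibility.
- **Counts may exist.** The CONSORT figure is not shown in the text available here and may report removals by arm.

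Three stronger readings are tempting, but the documents do not support them.

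- **That the window is longer for controls.** A reader might infer this because the single meeting is described only under the intervention arm. But that meeting includes consent and randomisation, which come before an arm is known, and the timing of the control baseline is simply unstated.
- **That staff who know the allocation make the removal decision.** No section says who performs the re-check. The supportable statement is that no arm-blind decision is described.
- **That the bias could approach half of the 14-point target.** This needs a control rate of about 40% (0.10 × 0.60 / 0.90 = 6.7 points), which is outside the 65% to 78% that the protocol assumes.

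**Conclusion.** The concern holds in a limited form. The stated removal rule contradicts the stated intent-to-treat analysis, and as worded it discards some primary-outcome successes. That follows from the text and needs no assumption about numbers.

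The size is unknown. With the protocol's control rates, no true effect, and removals confined to controls who would all have succeeded, the spurious difference is 1.2 to 1.8 points at 5% removal and 2.4 to 3.9 points at 10%. Against the matching planned effects, 10% removal is 2.4/14 = 17% or 3.9/17 = 23%. Both the removal share and its one-sidedness are assumptions. Unequal removal between arms has not been shown, and removal mainly from the intervention arm would shrink the effect.

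The rule should still be corrected before analysis, because it acts directly on the primary endpoint and the remedy is cheap. According to the Results section, follow-up runs to February 2026 and results are expected in March 2026.

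**What to change.** 1. **Restrict exclusion.** For people already randomised, exclude from the primary analysis only when a documented screening date precedes the randomisation date and shows that the person was ineligible. Someone blind to arm should decide, with the same evidence rule in both arms.
2. **Restore the rest.** Return anyone screened on or after randomisation to the assigned arm and count the screening as an outcome.
3. **Report and test.** Report removals by arm, reason and screening date. Add a sensitivity analysis on all randomised participants. Treat removed people without outcome data under the dropout scenarios already in the Analysis Plan (missing completely at random, all responders, all nonresponders).
4. **Any remaining or future enrolment.** Complete the nonadherence check and baseline before the arm is released. Recruitment is reported as running until August 2025, so this step cannot repair assignments already made.

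The cost is a wording change and retrieval of records, which were moved to a separate database and so should be traceable. No follow-up of removed people is described, so some outcomes may be missing. A few truly ineligible people will also appear in the all-randomised sensitivity analysis.
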